### Clinical outcomes

#### Body composition

The primary endpoint is change in lean body mass (LBM) which will be assessed after 12 weeks of PRT or control using Dual Energy X-ray Absorptiometry (DXA) (Herlev site: GE lunar iDXA, GE Healthcare Technologies; Aarhus site: Hologic QDR-series, Hologic Inc., Bedford, MA, USA). The hypothesis is that 12 weeks of progressive resistance training can attenuate the loss of LBM by at least 25%. This time span was chosen since 12 weeks are considered a sufficient period of PRT needed to affect LBM. Furthermore, this time point is a usual evaluating point for head and neck cancer as it coincide with the 2-month post-radiotherapy follow-up. Changes in total body mass and fat mass will also be assessed. Total body weight, with patients in light clothing and no shoes, will be measured weekly by the same digital scale at each site during therapy and bi-weekly thereafter.

#### Adherence

Adherence to the PRT program is registered by the physiotherapist or educated training instructors. Adherence to the study in general is encouraged by highlighting the importance of both groups in order for the trial to produce valid results. Furthermore, most appointments are planned when patients already have an appointment at the hospital, making it as convenient as possible for the patients.

#### Maximal muscle strength

All physical tests are conducted by the physiotherapist or the training instructors. Muscle strength will be evaluated by 1RM test of unilateral leg press (dominant leg) and bi-lateral chest press performed in the conventional equipment used in training. One RM tests are widely used when evaluating changes in maximal muscle strength in cancer patients [34, 35]. Following an exercise specific warm up, the patient will have one attempt with a given load, which will gradually be increased until the patient is unable to lift the load throughout a standardized range of motion using proper technique. As few attempts as possible will be used and a two-minute rest is ensured between all attempts to limit the risk of muscular fatigue.

#### Functional performance

Functional performance resembling activities of daily living will be evaluated using the 30 s chair stand test, 30 s arm curl test, and maximal stair climbing performance, best of two attempts. These are frequently used in cancer patients, including patients with HNSCC [20].

#### Treatment side-effects

Adverse events will be monitored according to Common Terminology Criteria for Adverse Events (CTCAE) version 4.0 [36], performance status will be registered according to ECOG scale, and pain using the Numeric Rating Scale (NRS) for pain, consisting of 11 points from 0 (no pain) to 10 (worst pain imaginable) [37].

#### Cytokine analyses, standard blood samples, and NK-cells

Standard blood samples will be taken according to schedule (Table 3). Blood samples for cytokine analyses will be taken before and after training sessions according to schedule (Table 3). Based on comprehensive explorative analyses with samples from a primary cohort of patients ([name] et al., manuscript submitted), we have identified a list of particularly interesting cytokines and other molecules for further analyses, including 6Ckine/chemokine (C-C motif) ligand 21 (CCL21), cutaneous T cell-attracting chemokine (CTACK)/CCL27, interleukin 6 (IL-6), IL-8/CXCL8, IL-15, IL-16, monocyte chemoattractant protein 1 (MCP-1)/CCL2, MCP-2/CCL8, macrophage-derived chemokine (MDC)/CCL22, macrophage migration inhibitory factor (MIF), macrophage inflammatory protein-1α (MIP-1α)//CCL3, thymus-expressed chemokine (TECK)/CCL25, tumor necrosis factor α (TNF-α), soluble epidermal growth factor receptor (sEGFR), basic fibroblast growth factor (FGF-basic), follistatin, hepatocyte growth factor (HGF), leptin, platelet-derived growth factor AB/BB (PDGF-AB/BB), prolactin, stem cell factor (SCF), soluble vascular endothelial growth factor-1 (sVEGFR-1), and sVEGFR-2. In initial analyses some of these cytokines increased during CCRT whilst others decreased, and the interesting point would be to investigate if PRT may affect these changes in either direction. Furthermore, the mobilization of NK-cells during PRT will be evaluated in week 3 and 12. The frequency and cytotoxic profile of the NK-cells will be analyzed by flow cytometry by staining for the surface receptors CD3, CD16 and CD56, as well as intracellular expression of Granzyme B and Ki-67.

#### Muscle biopsies

Muscle biopsies are optional for patients, but if accepted, they will be collected under sterile conditions from the middle lateral part of the vastus lateralis muscle using a 5 mm Bergstrom biopsy cannula preceded by local anesthesia (lidocaine 10 mg/ml). Both satisfactory thrombocyte count (≥ 40 × 10^9^/L) and International Standard Ratio (≤ 1.5) will be confirmed. Biopsies are taken from the mid-thigh of the same leg but a few centimeters from the previous biopsy at each time point to avoid variation between legs in the analyses. The samples will be dissected to be free of visible fat and connective tissue. A well-aligned portion of the biopsy for muscle fiber morphology analyses will immediately mounted in Tissue-Tek (Qiagen, Valencia, CA) and frozen in isopentane precooled in liquid nitrogen. The rest of the biopsy for later proteomics analyses will be frozen directly in liquid nitrogen. All samples will be stored at −80 °C until analysis.

The muscle biopsies are planned to be used for investigating differences in changes in muscle fiber types, protein expression, and metabolic pathways between the two groups.

### Questionnaires

#### Physical activity

To register PA in addition to the supervised training of the PRT group as well as all PA in the control group, patients will fill in a weekly trial specific questionnaire on PA. Thus, type of activity (running, resistance training, walking etc.) and the daily duration of the activity will be registered every week from baseline to the end of the training period. Also, patients will fill in a physical activity scale (PAS) questionnaire for measuring average weekly PA of sleep, work, and leisure time [38].

#### Energy intake

Patients will receive dietary counseling by clinical dietician before or immediately after start of treatment as well as by educated nurses during the treatment period. If patients are admitted due to nutritional issues during the treatment period, they will be seen by a clinical dietician. Resting metabolic rate (RMR) will be estimated using the Mifflin-St. Jeor formula described elsewhere [39]. Energy expenditure (kilojoules per day) is measured as: Energy need (kJ) = RMR x activity factor × 4.184. Activity factor will be based on self-reported PA at the different time points. Protein need will be estimated as 18% of total energy need: Protein need (gram) = (total energy need (kJ) × 18)/17. A clinical dietician will calculate total daily energy intake based on patient reported information from a questionnaire filled in weekly during treatment (Table 3). The number of patients needing tube feeding and the duration of the tube feeding will also be registered.

#### Quality of Life (QoL)

Changes in QoL will be evaluated using the European Organisation for Research and Treatment of Cancer (EORTC) quality of life questionnaires, QLQ-C30 and QLQ-H&N-35, which have previously been used in exercise studies in cancer survivors [40] and in Danish HNSCC patients [41].

#### Satisfaction with the program

A semi-structured questionnaire was developed asking patients to grade the effect the program have had on their physical, psychological, and social well-being on a scale from 1 to 10, 1 being “very positively”; 10 being “very negatively”. Furthermore, patients are asked if scheduling was convenient and whether the PRT program was appropriate, too hard or too light (training group only). In addition, they can make free text on all questions.

#### Work

Affiliation to work market will be registered as a measure of convalescence, measuring how soon patients return to work and to what extent. At 2, 6, and 12 months follow-up patients fill in a questionnaire with information about current work status, date when work was resumed, and at 2 months follow-up, also, educational status, occupation, and work hours prior to diagnosis will be registered.

### Blinding procedures

Assessment of the primary endpoint (LBM) will be blinded since the personnel performing DXA scans will not be aware of randomization status of the patients. Due to practicalities physical tests cannot be blinded. However, tests are standardized and performed by the same personnel regardless of randomization. Personnel analyzing blood samples and muscle biopsies are blinded to patient identity and group allocation.

### Statistical considerations

The primary endpoint is difference in mean change of LBM between the training and the control group, specifically, whether attending this particular PRT program can significantly attenuate the loss of LBM after 12 weeks of PRT, which approximately aligns with the time where the treatment is evaluated (2 months after end of radiotherapy). Thus, the time at which the primary endpoint is evaluated is at 12 weeks after initiation of PRT.

The second important decision was to define a clinically meaningful endpoint in terms of difference in change in LBM loss. Of course, the 12 week period in which it was possible to train was included as a parameter since the short training period would influence the possible outcome, and even more so as patients were expected to lose LBM as a result of side effects to treatment. Limited clinical data were available on the possible effect of a 12-week PRT program on LBM change during concomitant chemoradiotherapy, though Lonbro et al. did find that head and neck cancer patients attending a 12-week PRT program initiated after radiotherapy gained an average of 2.3 kg (95% CI 1.7–3.0) [20]. A similar effect can probably not be expected when PRT is performed during chemoradiotherapy as the patients during this time are in a catabolic state. This was seen in our pilot study where patients despite PRT had a mean LBM loss of 3.6 kg ([name] et al., manuscript submitted).

Based on these deliberations we concluded that a difference of 25% in LBM loss between the exercise group and the control group (which, estimated from data in the pilot study, would be 1.2 kg of LBM in absolute difference) would be a clinically meaningful difference, and yet, an obtainable goal in the circumstance of undergoing CCRT.

Thus, the sample size calculation is based on changes in LBM in our one-armed pilot study where a 3.6 kg reduction (corresponding to 6.8%) in LBM was detected after 12 weeks of PRT ([name] et al., manuscript submitted). A priori, a sample size of 34 in each group will have 80% power to detect a difference in means of 25% ((9.06%–6.8%)/9.06%) between the two groups (corresponding to an estimated mean LBM loss of 6.80% from baseline in the training group and an estimated LBM loss of 9.06% in the control group with a standard deviation of 3.27). A two group t-test with a 0.05 two-sided significance level was used.

An anticipated drop-out rate of 5% is included in the calculations to ameliorate the risk of inadequate patient number for analyses, hence 36 patients are planned to be enrolled in each group (total *n* = 72). Patients dropping out before or during the first week of treatment will be replaced by another patient.

Analyses will include descriptive analyses as well as mixed model repeated measures analyses examining differences between groups and over time. The α-level of statistical significance will be set to 0.05.

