### Randomization

Patients will be stratified by site (Herlev/Aarhus), sex (male/female), p16-status of the tumor (positive/negative) and BMI (<30/≥30) and randomized 1:1 to either a training group performing a 12-week PRT program or control group. If a patient leaves the study within the first week, the number of patients randomized will be increased by one. Patient inclusion form is faxed to The Danish Head and Neck Cancer (DAHANCA, Aarhus, Denmark) group administration, that performs the randomization using a software randomization file (developed and used by the DAHANCA group) that automatically and randomly allocates each patient in either group. The personnel conducting the randomization are independent of clinical personnel and are not otherwise involved in the study.

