Rest between sets	45–60 s
Rest between repetitions	0 s
Range of motion	Maximum possible
Rest between training sessions	Training every other day

Abbreviations: *PRT* progressive resistance training, *RM* repetition maximum, e.g. 15 RM is the heaviest load that can be lifted 15 times using proper technique. Sec, seconds

The PRT program starts concurrently with CCRT. 36 training sessions are planned, i.e. thrice weekly for 12 weeks, thus continuing approximately 6 weeks further than CCRT. If a session is cancelled due to treatment related interventions, radiotherapy, scans, or due to public holidays, the session will be replaced at the end of the training program. Sessions missed for personal reasons or incapacitation will not be substituted. It will be ensured that the PRT program and tests never compromise treatment schedule.

At the Herlev site conventional exercise equipment is used for all exercises but due to different equipment available at the involved sites, three specific exercises differ but with only minimal difference in target muscle groups or progression options. Thus, at the Aarhus site sit-ups will be performed as traditional floor exercises with free weights ensuring possible progression in intensity. Hamstring curls will be performed using elastic bands (TheraBand, The Hygenic Corporation, Ohio, USA) with varying resistance and lateral pull down replaces low seated row in Aarhus. Conventional resistance training machines (Technogym, Gambettola, Italy) are used at both sites.

During the first 6 weeks all training sessions are supervised by physiotherapist or educated training instructors. When possible the same supervised training modality at the hospital training facility will continue for the remaining 6 weeks. If a patient is unable to attend training sessions at the hospital, e.g. due to prolonged transport time, the remaining training sessions will be tailored individually at commercial training facilities near the patients’ own home. However, patients must attend at least one session per week supervised at the hospital training facility.

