### Controls

No restrictions on physical activity (PA) or other concomitant care are made for the control patients but no organized training will be offered to them. PA is reported in training logs. Except for blood sampling which, obviously, will not be drawn after any training session (see below) in the control group, there are no differences in tests and assessments between the groups.

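### Randomised patients who leave before or during week 1 are replaced when they already know their arm, and the plan does not say they are followed or kept in the comparison

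*Protocol article*

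**What the plan says.** The rule appears twice in the protocol article.

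- Randomization: "If a patient leaves the study within the first week, the number of patients randomized will be increased by one".
- Statistical considerations, directly after the 5% drop-out allowance: "Patients dropping out before or during the first week of treatment will be replaced by another patient".

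The Randomization section has patients "randomized 1:1 to either a training group performing a 12-week PRT program or control group". On the timing of the intervention, the Intervention section says: "The PRT program starts concurrently with CCRT". Of the control patients, the Controls section says that "no organized training will be offered to them". Under Blinding procedures, the personnel described as blinded are those performing the DXA scans and those analysing blood samples and biopsies. Patients are not.

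The article plans mixed model repeated measures analyses and names no analysis population. It does not say whether a replaced patient stays in the analysis, appears in the patient flow, or is asked to return for the week-12 scan.

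**The concern.** The rule is triggered by something that happens after randomisation, at a time when the patient knows the arm. Because training begins with chemoradiotherapy, the first treatment week is also the first week of living with the allocation. A control patient may leave out of disappointment. A patient in the training arm may leave because three sessions a week come on top of six radiotherapy fractions and weekly chemotherapy, a burden that the Discussion itself recognises. Either reason could be related to later loss of lean body mass (LBM).

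If such patients are set aside and others counted in their place, the analysed arms are selected by an event that allocation may have influenced. The bias could go either way. Losing training-arm patients who would have done badly flatters the programme, and so does losing motivated controls who would have done well. The opposite patterns would hide an effect. With 36 patients planned per arm, a handful is enough to matter.

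The two sections also word the window differently. Randomization counts a first week without saying from when. Statistical considerations counts the first week of treatment and adds the time before it.

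**Working it through.** **1. The plan's own sample size.** Inputs from Statistical considerations: "estimated mean LBM loss of 6.80% from baseline in the training group and an estimated LBM loss of 9.06% in the control group", SD 3.27, 80% power, and the test: "A two group t-test with a 0.05 two-sided significance level was used".

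- Target difference: 9.06 − 6.80 = 2.26 percentage points. Relative to control, 2.26/9.06 = 24.9%, stated as 25%.
- The exact two-sample t-test calculation gives 33.85, so 34 per group, with power 80.2% at 34.
- Drop-out of 5%: 34/0.95 = 35.8, so 36 per group and 72 in total.

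The stated figures reproduce. The replacement rule plays no part in them; the 5% allowance is separate.

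**2. What the two sections establish together.** Randomization shows that the leaver has already been randomised and that the number randomised rises by one. It adds a randomisation and does not put a substitute in the leaver's arm. Statistical considerations calls this replacement. Neither says what becomes of the leaver's data.

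**3. Size if leavers are left out.** The documents give no figures here, so these are assumptions: k leavers, all from one arm; 36 stayers in that arm; the leavers' mean LBM change would have differed from the stayers' by D, taken as 0.5 SD (1.635 points) to 1 SD (3.27 points). The arm mean over everyone randomised to it differs from the stayers' mean by

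bias = D × k/(36 + k).

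| k | k/(36 + k) | bias, D = 0.5 SD | bias, D = 1 SD | share of 2.26 |
|---|---|---|---|---|
| 2 | 2/38 = 0.053 | 0.09 | 0.17 | 4% to 8% |
| 4 | 4/40 = 0.100 | 0.16 | 0.33 | 7% to 15% |
| 6 | 6/42 = 0.143 | 0.23 | 0.47 | 10% to 21% |

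**4. Effect on the test when there is no true difference.** With 36 analysed per arm, the standard error is 3.27 × √(2/36) = 0.77. Biases of 0.17, 0.33 and 0.47 points give noncentrality 0.22, 0.43 and 0.61. On 70 degrees of freedom the two-sided rejection rate is then about 5.5%, 7.1% and 9.2%, against a nominal 5%.

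**5. Which part of a remedy does the work.** Suppose nobody were replaced and k of 36 simply had no outcome. The shift would be D × k/36; for k = 4 and D = 1 SD that is 3.27 × 4/36 = 0.36 points, no smaller than the 0.33 above. So the harm comes from the missing outcome and not from the extra randomisation. If two of four leavers are scanned at week 12 and a simple mean is taken, the remaining bias is 3.27 × (4/40 − 2/38) = 0.15 points, about half of 0.33. If all are scanned and analysed by allocated arm, it is zero.

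**The case against.** The strongest reply is that the article nowhere excludes these patients. A reader might infer that the rule drops patients and breaks the randomised comparison, but that goes beyond the text. The Randomization section only increases the number randomised, which leaves the leaver among those randomised. The 72 is planned enrolment, not a defined analysis set. The article condenses a fuller protocol, and a statistical analysis plan may define the analysis population, so the lack of an intention-to-treat statement is no defect by itself. All of this stands, and it is why the point is conditional.

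Three further stronger readings fail.

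- A reader might infer that adherence is flattered because early refusers of training vanish. The rule concerns leaving the study. Under Intervention, a patient who feels unable to train has the programme paused, and nothing says such a patient is replaced.
- A reader might assume larger differences, say 4 to 6 points. That is 1.2 to 1.8 times the SD of 3.27, and nothing in the documents supports it.
- A reader might say that replacement double-counts the 5% allowance. Topping up for very early losses alongside an allowance for later ones is a legitimate design choice.

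It is also fair that the difference in window is small. Training and treatment start together, so the wordings part mainly over the time between randomisation and treatment start.

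What the reply does not remove is a stated rule, acting after allocation is known, whose natural reading is that one patient takes another's place, with no provision for following the one who left.

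**Conclusion.** The point holds in conditional form. The plan replaces randomised patients who know their arm and leave before or during week 1, and it does not secure their follow-up or their place in the comparison. If they are left out, the bias is about 0.09 to 0.47 percentage points, or 4% to 21% of the target difference. That range rests on 2 to 6 leavers, all from one arm, differing by 0.5 to 1 SD, none of which comes from the documents. The upper end is demanding: 6 of 42 is 14% of one arm lost by week 1, whereas the plan expects 5% drop-out. Leavers spread evenly over the arms and alike in outcome would produce little net bias, and the bias is zero if all are followed and analysed.

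This should be fixed. It does not show that the primary comparison is invalid as planned. The sample size is unaffected.

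**What to change.** Put the same text under Randomization and under Statistical considerations, to this effect:

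> Extra patients may be randomised to compensate for early withdrawal, but no randomised patient is removed. All randomised patients are analysed in their allocated arm and shown in the patient flow. Those who leave early are invited, where they consent, to the planned week-12 DXA.

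Use one definition of the window in both sections, with its starting point stated. Report any analysis that omits first-week leavers only as a sensitivity analysis.

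The invitation to the scan is the part that counts. A leaver kept in the mixed model with only a baseline value contributes little and leaves most of the bias in place. It should be settled while the trial is running, because a week-12 scan that was not sought cannot be obtained later.

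The cost is a change of wording, slightly more follow-up effort, and a few missing week-12 values from patients who decline. The scan is already in the schedule, and the target of 34 analysable patients per group stays as it is; k early leavers make the randomised total 72 + k.

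### Randomisation is stratified on four factors, but the analysis sentence names only group and time and no scale is fixed for the primary test; run as worded, it would be somewhat conservative

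*Protocol article*

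**What the plan says.** All references are to the protocol article.

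- **Randomization:** "Patients will be stratified by site (Herlev/Aarhus), sex (male/female), p16-status of the tumor (positive/negative) and BMI (<30/≥30"), with allocation 1:1. Four two-level factors make 16 cells, or 72/16 = 4.5 patients per cell on average.
- **Body composition:** LBM is measured on two makes of scanner, "Herlev site: GE lunar iDXA, GE Healthcare Technologies; Aarhus site: Hologic QDR-series". Scanner make and site are therefore the same variable.
- **Statistical considerations, endpoint:** "The primary endpoint is difference in mean change of LBM between the training and the control group", evaluated at 12 weeks. No unit is attached.
- **Statistical considerations, sample size:** a two-group t-test on percent of baseline, with losses of 6.80% and 9.06% and an SD of 3.27. The 25% relative difference is also expressed in kilograms: it "would be 1.2 kg of LBM in absolute difference".
- **Statistical considerations, analysis:** "Analyses will include descriptive analyses as well as mixed model repeated measures analyses examining differences between groups and over time". This is the only sentence on the model. It names no covariate and excludes none.

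**The concern.** Stratifying makes the arms alike on the chosen factors, so the estimated treatment effect varies less from trial to trial. A model that leaves those factors out still counts their variance as residual noise. Its standard error then overstates the true uncertainty, the test rejects too rarely, and precision that the design has secured goes unused. Baseline LBM is not a stratification factor, but it is measured in every patient and can be used in the same way.

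The scale bears on the same question. If percent loss is unrelated to body size, kilogram loss grows with body size. An unadjusted kilogram analysis then carries variance that the percent scale used for the power calculation does not. In a trial of 72 patients planned at 80% power, either loss is worth avoiding.

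**Working it through.** **1. The plan's own figures.** Difference 9.06 − 6.80 = 2.26 points; SD 3.27; two-sided 0.05. The noncentral t gives n = 33.85, so 34 per group, with power 80.2%. With 5% drop-out, 34/0.95 = 35.8, so 36 per group and 72 in total. The stated numbers reproduce.

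**2. Percent and kilograms.** The pilot loss of 3.6 kg is 6.8%, so baseline LBM is 3.6/0.068 = 52.9 kg. Then 2.26% × 52.9 = 1.20 kg, and 3.27% × 52.9 = 1.73 kg for the SD. The 1.2 kg is a consistent translation.

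**3. Effect of adjustment.** R² is the share of variance in change explained by the four factors and baseline LBM together. It is not in the documents, so the range is assumed.

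- Unadjusted SE = 3.27 × √(2/34) = 0.793.
- Adjusted SE = 0.793 × √(1 − R²).
- Ratio of unadjusted to adjusted SE = 1/√(1 − R²).

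| Assumed R² | Adjusted SE | Unadjusted SE too wide by | Power with adjustment, n = 34 per arm |
|---|---|---|---|
| 0 | 0.793 | 0% | 80.2% |
| 0.05 | 0.773 | 2.6% | 82.1% |
| 0.10 | 0.752 | 5.4% | 84.1% |
| 0.20 | 0.709 | 11.8% | 88.1% |
| 0.30 | 0.664 | 19.5% | 91.9% |

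Using 61 instead of 66 degrees of freedom lowers each power by about 0.1 point (80.2% becomes 80.1% at R² = 0).

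The gain over an unadjusted test is smaller than the distance from 80%, because balance helps the unadjusted estimate too. If the predictive variables were perfectly balanced, unadjusted power would be about Φ(2.26/SE_adj − 1.997 × ratio), which is 81.6%, 83.0% and 84.6% at R² 0.10, 0.20 and 0.30. Baseline LBM is not balanced by design, so the true figure lies between 80.2% and these values.

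**4. Type I error by simulation.** 4,000 runs per setting; 68 patients; 16 cells; permuted blocks of 4 (assumed, since the article gives no block size); kilogram change. The adjusted model has the four factors and baseline LBM. The spread of baseline LBM is assumed. Here R² is varied from 0 to 0.30.

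| R² | Type I, unadjusted | Type I, adjusted | Power, unadjusted | Power, adjusted |
|---|---|---|---|---|
| 0 | 4.8% | 4.7% | 74% | 78% |
| 0.10 | 3.9% | 4.7% | 76% | 83% |
| 0.20 | 3.3% | 4.5% | 76% | 86% |
| 0.30 | 2.9% | 4.9% | 77% | 90% |

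Monte Carlo error near 5% is about ±0.7 points. Part of the power gain comes from baseline LBM, as the row for R² = 0 shows.

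**5. Unadjusted kilograms.** Assume that percent loss p is independent of baseline B. Then Var(kg change) = (52.9 × 0.0327)² + Var(B) × (m² + 0.0327²), with m² = (0.068² + 0.0906²)/2. For an assumed coefficient of variation of B of 10%, 15% and 20%:

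- SD is 1.79, 1.86 and 1.96 kg, against 1.73 kg.
- Baseline explains about 6%, 12% and 19% of the variance.
- Power for 1.20 kg is 77%, 74% and 70%.

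**6. Scanners.** A constant offset cancels in within-patient change: with a simulated 3 kg offset the estimate was 1.21 kg. Suppose a proportional gap of 5% or 10% (assumed), equal enrolment at the two sites, and a mean loss of (3.6 + 4.8)/2 = 4.2 kg.

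- Pooled effect = 1.20 × (1 + gap/2) = 1.23 or 1.26 kg, a shift of 0.03 to 0.06 kg.
- Site difference in mean loss = 0.21 or 0.42 kg. Its share of variance is (0.21²/4)/(0.21²/4 + 1.73²) = 0.4%, or 1.5% for 0.42 kg.
- Simulated type I error stayed at 4.8% to 5.1%.

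A purely proportional gap cancels in percent change.

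**The case against.** The strongest reply is that silence is not exclusion. The sentence says what the analyses will include, and the article condenses a fuller protocol. Covariates may well be listed there or in an analysis plan. This stands: the article names only group and time, but a reader cannot conclude that the trial will use only those terms. It is also true that every R² here is assumed, that part of the gain is due to baseline LBM and not to stratification, and that the sample size was set without relying on adjustment.

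Three stronger readings are tempting, and the documents support none of them.

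- **The error bars are wrong as a matter of fact.** They are too wide only if the variables predict change. The direction is conservative, so there is no added false-positive risk.
- **Pooling two makes of scanner biases the result.** The endpoint is change within patient, each site has one scanner make, and stratifying by site keeps make roughly balanced between arms. The plausible shift is a few hundredths of a kilogram.
- **The kilogram and percent figures conflict.** They agree. What is open is which of them the primary test uses.

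What remains is that the published text ties neither the model nor the scale to the design, and that using variables already collected can only help appreciably or cost almost nothing.

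**Conclusion.** The point holds as an improvement to the analysis and not as an error in a stated figure. If the model is run with group and time alone, the loss runs from none at R² = 0, through standard errors about 5% too wide at 0.10, to about 20% too wide at 0.30. Adjusted power at 34 per arm is 80%, 84% and 92% at those values. These results rest on the assumed R², on the planned difference and SD being right, and, for the type I figures, on the assumed block size. The choice of scale adds to the case: kilograms without baseline adjustment could fall below the planned power if kilogram loss rises with body size. Scanner make is a minor further reason to include site and to work in percent.

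**What to change.** State the primary analysis in one or two sentences, in the analysis plan or an amendment made before the data are compared by group:

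- In the mixed model for repeated measures, the primary contrast is the week-12 difference between groups.
- The outcome is percent change in LBM from baseline, the scale of the power calculation. Kilogram change is reported as supportive.
- The covariates are baseline LBM, site (which carries scanner make), sex, p16 status and BMI class (<30/≥30).

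This uses five degrees of freedom of 66, about 0.1 point of power if the covariates predict nothing, and needs no new data. Modelling log LBM, adding a baseline-by-site term, or stating that each patient stays on one scanner are optional refinements.
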